## Abstract

**Background:**

As in other countries worldwide, the prevalence of mental disorders in Germany is high. Although numerically a dense network of in- and outpatient psychiatric health services exists, the availability in rural and remote regions is insufficient.

In rural regions, telemedical concepts can be a chance to unburden and complement the existing healthcare system. Telemedical concepts consisting of video or telephone consulting show first positive results, but there are only a few studies with a randomized controlled design.

To improve the treatment of patients with mental disorders in rural regions, we developed a telemedical care concept based on telephone contacts and text-messages. The primary objective of this study is to evaluate the effects of the telemedical interventions on psychopathological outcomes, e. g. anxiety, depressive symptoms, and somatisation. Secondary objective of the study is the analysis of intervention effects on the frequency of medical contacts with healthcare services. Furthermore, the frequency of patients' crises and the frequency and kind of interventions, initiated by the project nurses will be evaluated. We will also evaluate the acceptance of the telemedical care concept by the patients.

**Methods/Design:**

In this paper we describe a three-armed, randomized, controlled study. All participants are recruited from psychiatric day hospitals. The inclusion criteria are a specialist-diagnosed depression, anxiety disorder, adjustment disorder or a somatoform disorder and eligibility to participate in the study. Exclusion criteria are ongoing outpatient psychotherapy, planned interval treatment at the day clinic and expected recurrent suicidality and self-injuring behaviour.

The interventions consist of regular patient-individual telephone consultations or telephone consultations with complementing text-messages on the patients' mobile phone. The interventions will be conducted during a time period of 6 months.

**Trial registration:**

This study is registered in the German Clinical Trials Register (DRKS00000662).

## Background

### Epidemiology and utilization of health care services

Surveys and cohort studies have shown that mental disorders have high prevalence rates in the general population worldwide. For example the representative National Comorbidity Survey Replication in the USA with over 9 000 participants showed a lifetime prevalence of 46.4% for any mental disorder, thereof 28.8% for anxiety disorders and 20.8% for mood disorders [1].

In Germany, the German Health Interview and Examination Survey (GHS) revealed similar results. A lifetime prevalence of 43% for any disorder was found, thereof the most frequent mental diseases were anxiety, mood, and somatoform disorders [2]. The German Federal Health Survey of 1998 (Bundes-Gesundheitssurvey) showed a lifetime prevalence of 19% for depression [3]. The German findings are comparable to those in other European countries [4].

In Germany, health care in the field of mental diseases consists of psychotherapeutic practices for outpatient care, specialised clinics or departments in hospitals for inpatient treatment, and also day care hospitals, psychiatric walk-in clinics, and other psychiatric information and consultation centres are established [5].

However, regarding the availability of outpatient psychotherapists, there are large regional differences. The number of inhabitants per psychotherapist fluctuates between 2577 in cities and 23106 in rural regions [5]. Consequences are long waiting lists, e.g. for a continuation of treatment after delivery from a psychiatric hospital or day hospital.

As shown in several studies, treatment rates are fairly low. In their review of 27 studies, covering 16 European countries, Wittchen and Jacobi found that only 26% of all patients had any contact with health care services [4]. In Germany, the German Health Interview and Examination Survey showed health care utilization of 30% for patients without co-morbidity and 76% for highly co-morbid patients [2]. In the cohort "Study of Health in Pomerania" (SHIP) [6], which is conducted in the study region Western Pomerania, a treatment rate of 20% was estimated [7].

Mental disorders are associated with increased usage of healthcare services [8]. In the SHIP-cohort, depression and somatisation and a combination of depression, somatisation, and anxiety were predictors for considerable increases of inpatient and outpatient costs between baseline and 5-year follow-up [9].

### Telemedical concepts for mental healthcare

To improve the treatment of patients with mental disorders, especially in rural regions, telemedical concepts can be a chance to unburden and complement the existing healthcare system.

In the last years, several studies to evaluate possibilities and limitations of telemedical concepts were applied in various countries. In some cases, videoconferences were conducted to enable contacts with psychotherapists. The results of a project in Canada, that evaluated the satisfaction of healthcare professionals with video consultations between patients in rural areas and general hospitals, were positive [10]. In a project on the Canary Islands, videoconferencing was established to provide psychiatric consultations for remote regions. Patients' acceptance and satisfaction with the concept were high. Video consultation was used mostly to confirm diagnoses of the local general practitioners and to get advice about case management of the patients [11]. In Australia, the feasibility of video consultations in child and adolescent psychiatry was evaluated. The results were positive, video consultations were seen as a flexible and effective service for patients with complex needs [12].

A randomized study from Ontario, Canada, analysed clinical outcomes of patients, who received telepsychiatric consultations compared to patients receiving face-to-face consultations. The clinical outcomes of both groups were equivalent [13]. Reviews of randomized controlled trials show, that videoconferencing can be a good alternative for face-to-face consultations, especially in rural regions. The acceptance among patients and psychotherapists is high, clinical outcomes are comparable with usual care [14-16].

Video consultations require a high level of organisation, special technical conditions, and financial investment. Telephone consultations are, technical, organisational, and financial, less demanding but maybe perceived as more impersonal as video consultations. An advantage is the broad and permanent availability of mobile phones, which can be beneficial in crisis situations.

Hilty et al. describe a concept of using telephone consultation and e-mail contacts. The participating patients showed clinical improvement, the providers were satisfied with the concept [17].

Another (non-randomized) study (cognitive behavioral therapy-telephone treatment (CBT-TT)) evaluated telephone-psychotherapy for patients with depression, which initiated a treatment at a mental health clinic. After 3 and 6 months, there was a significant reduction in depression severity [18].

In a randomized controlled trial, among others, telephone therapy was compared with usual care with patients with depressive disorders, starting their therapy. The telephone psychotherapy intervention resulted in a significant reduction of depression severity [19].

Rollman et al. examined whether telephone-based collaborative care can improve clinical outcomes for panic and generalized anxiety disorders compared to usual care provided by primary care physicians. After 12 months, both anxiety and depressive symptoms improved [20].

A randomized controlled trial in Germany, conducted in GP-practices, found a significant decrease of the severity of depression symptoms. In this trial, structured telephone interviews to assess depression symptoms were made by practice assistants [21].

Although Germany has large rural regions with an insufficient availability of outpatient psychotherapeutic healthcare services, the awareness of the potentially beneficial contribution of telemedical consultations in this field is still poorly developed.

The study outlined in this paper is based on collaboration between the Clinic of Psychiatry and Psychotherapy and the Institute for Community Medicine, both located at the University of Greifswald in the region of Western Pomerania in Germany. A telemedical centre is affiliated with the Institute for Community Medicine. Here, telemedical concepts for various indications and patients groups are developed, implemented, and evaluated [22].

Western Pomerania is a rural region in the Northeast of Germany at the Baltic Sea coast. Psychotherapeutic healthcare services are concentrated in the larger towns. After treatment in a psychiatric day hospital, patients have to wait up to 6 months for further treatment in a regular outpatient psychotherapeutic practice.

To bridge this long waiting period, we developed a telemedical concept consisting of regular, patient-centred telephone consultations and text-messages on the mobile phone, conducted by nurses of the University Hospital of Greifswald.

The intention of this concept is to ensure a low-threshold continuous telemedical care beyond discharge from a psychiatric day hospital, to attend to patients` crises timely and to initiate necessary interventions.

## Research objectives

The primary objective of this study is to evaluate the effects of the telemedical interventions on psychopathological outcomes, e. g. anxiety, depressive symptoms, and somatisation.

Secondary objective of the study is the analysis of effects of the interventions on the frequency of medical contacts with healthcare services, both psychotherapeutic and in other medical fields.

Furthermore, we will evaluate the frequency of patients' crises, recognized by the project nurses, the frequency and kind of interventions, initiated by the project nurses, and also assess the kind of medication during the intervention.

We will also evaluate the acceptance of the telemedical care concept by the patients.

## Methods/Design

### Study design

This study is a three-armed, prospective, controlled, randomized trial. Two of the study arms include an intervention (regular telephone contacts and telephone contacts with additional text-messages), the third arm is a control group. The interventions will be conducted during a time period of 6 months after discharge. Importantly, the interventions outlined below are all applied in addition to the individual outpatient treatment provided. Therefore, also the control group receives outpatient treatment (e.g. medication, short interventions by any GP or psychiatrist).

The outcomes described in the section research objectives will be compared between all three groups.

### Recruiting and participants

It was planned to recruit a total of 90 patients, 30 in each arm of the study. The recruitment started September 2009. As the first participants were contacted to have their final interview after 6 months, the loss to follow up in the control group was about 20%. Therefore, we decided to continue the recruitment until a total of 120 participants included.

All participants are recruited from three psychiatric day hospitals in the region of Western Pomerania in the Northeast of Germany. The treating psychiatrists and psychotherapists select eligible patients before their discharge from the day hospital. The patients are informed about the project and are asked to provide informed consent.

The inclusion criteria are:

- a diagnosed depression, anxiety disorder, adjustment disorder or a somatoform disorder;

- eligibility to participate in the study, attested by the treating psychiatrist or psychotherapist.

Exclusion criteria are

- interval patients, defined as patients who return to the day hospital after 3-6 months to continue their therapy;

- patients who show a distinct emotional instability with recurrent suicide crises and self-injuring behaviour.

After the patients' agreement to participate in the study, the treating psychiatrist or psychotherapist from the day clinic completes a short standardized enrolment form with personal data of the patient (name, address, telephone number, date of birth), diagnoses, medication, and patients' individual therapy goals and/or themes, that were elaborated between the psychotherapist and the patient. Examples for therapy goals or themes are: exposure to critical factors (e.g. to use public transportation, to go shopping alone), to socialize with other people, to deal with family problems, to perform relaxation techniques regularly, to create a structural schedule for the day and the week, to concern about occupational rehabilitation. The enrolment form is transferred to the telemedical centre. Here, the patients are randomized to one of the three study arms.

### Study intervention

Two telemedical interventions of different intensity will be applied during a time period of 6 months. The intervention of the first arm of the study consists of regular telephone contacts, conducted by specially trained nurses. The first month, the telephone contacts take place once a week, thereafter, once a month. If necessary, the frequency of the telephone contacts can be increased. It is also possible for the patients to contact the nurses by telephone during office hours (8 am - 4 pm).

The first part of the telephone calls consists of standardized questionnaires to enable the monitoring of important parameters over time:

- The Brief Symptom Inventory (BSI) is a standardized questionnaire to assess the severity of relevant symptoms, e.g. feelings of loneliness, melancholia, panic attacks, restlessness, suicidal thoughts, pain in heart and chest, sickness [23].

- Contacts with physicians: assessment of the number of contacts with a general practitioner, an emergency physician, and various medical specialists and the reason for the last physician contact. Further, the patient is asked to evaluate his satisfaction with the contacts applying grades from 1 to 6.

- Inpatient stays: it is assessed whether the participants had inpatient stays in hospitals (separate for acute and planned admission), and rehab centres. The participants are asked for the number of stays, the total number of days, and the reason for admission. During the first telephone call, contacts with physicians and inpatients stays are assessed for the last 6 months, during the following contacts for the time since the last telephone contact.

- Standardized evaluation of the health situation of the participant by the nurse, it is possible to supplement this judgement by free text remarks.

The second part of the telephone call consists of asking for special or unusual occurrences and specific questions about the individual therapy themes as a guideline for the talk:

- Did anything special or unusual happen during the last weeks (e.g. regarding family, relationship, friends, job, health situation)? Was it positive or negative? Were you satisfied with your behaviour in or reaction on this situation?

- For each therapy goal or theme: in the day hospital, you formulated the following therapy goal or theme together with your psychotherapist. Could you work on it? Are you satisfied about how you worked on it (grade 1 to 6)? Do you think you can pursue this goal more intensively?

The third part of the telephone call deals with the medication of the participant. The following questions are asked for each drug separately:

- Do you take this drug in the same dosage as the last time we called (first telephone call: as you were discharged from the day hospital)? If no, why not? Did a physician change something about the dosage? If yes, what was changed?

- How do you assess the effect of this drug (free text)?

- How regular do you take this drug? Possible answers: always, mostly, rarely, never, don't know, don't want to answer

The telephone call is finalized by making an agreement about the next call and the question whether the patient wishes to include another topic.

The intervention of the second study arm consists of telephone contacts with the same content as the telephone contacts of the first study arm as described above. Additionally, once a week short text-messages are sent to the participating patients. These text-messages take up the individual therapy goals or themes (e.g. "Did you take the bus today?", Did your appointment with your boss go well?"). The participants can answer on these messages, and the nurses will react again if necessary or appropriate.

If the nurses recognize a (starting) crisis, they will increase the number of telephone contacts, make an appointment for a consultation with the treating psychotherapist or arrange a crisis intervention by the treating psychotherapist or by the hospital.

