### Evaluation Interviews

For the patients in the intervention arms of the study, evaluation data is collected mainly during the standardized part of the telephone calls (sociodemographic parameters, Brief Symptom Inventory, contacts with health services, medication assessment). Additionally, there is a short interview about acceptance of and satisfaction with the telemedical care concept [Table 1].

**Table 1 T1:** Interview questions to assess acceptance and satisfaction of the patients

Question:	How do you judge the telephone contacts during the last 6 momths?
Answers:	Very helpful - helpful - not helpful - other (free text) - I don't know - I don't want to answer
Question:	Would you be interested to continue the telephone contacts if possible?
Answers:	Yes - No - I don't know - I don't want to answer
Question:	Do you think, this kind of care can make face-to-face contacts less necessary or replace them partly?
Answers:	Yes - No - I don't know - I don't want to answer
Question:	Is there something you would change or improve?
Answer:	Free text

The patients of the control group have a baseline interview and a follow up interview after 6 months which includes the same standardized questionnaires as the intervention groups.

A flow chart of the study is shown in Figure 1.

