## Analysis

After finalizing the recruiting of the participating patients and conducting the interventions, the collected data will be analysed in a strictly pseudonymised way. Three kinds of analyses will be applied:

- The clinical outcomes of the patients (e. g. anxiety, severity of depressive symptoms, somatisation) and pharmaceutical problems in both intervention arms of the study will be statistically compared with the patients in the control group.

- The frequency of medical contacts with healthcare services, both psychotherapeutic and in other medical fields will be compared between the intervention arms of the study and the control group. This will also be analysed using secondary data from hospital-IT-systems of various hospitals within the region of Western Pomerania and the patients' statutory health insurances.

- Descriptive analysis of the frequency of patients' crises, the frequency and kind of interventions, initiated by the project nurses. For this evaluation, the contents of the telephone calls (documented in the project documentation system) and the text-messages have to be analysed and categorized.

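### Self-reported health-care contacts and inpatient stays are recalled over about 1 to 4.4 weeks in the intervention arms but about 6 months in the control arm, and no arm-neutral source is named as decisive

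*Protocol article*

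**What the plan says.** **Intervention arms.** The Study intervention section sets the timetable: "The first month, the telephone contacts take place once a week, thereafter, once a month". It adds: "If necessary, the frequency of the telephone contacts can be increased". For the reference period it says "During the first telephone call, contacts with physicians and inpatients stays are assessed for the last 6 months", and then "during the following contacts for the time since the last telephone contact". The Evaluation Interviews section confirms that these calls are the main data source: "evaluation data is collected mainly during the standardized part of the telephone calls", and it lists contacts with health services and medication among those data.

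**Control arm.** The same section says: "The patients of the control group have a baseline interview and a follow up interview after 6 months". These interviews use the same standardized questionnaires. No separate recall period is given for controls.

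**Analysis.** The frequency of contacts is the secondary objective, and the Analysis section compares it between the intervention arms and control. On routine data it adds: "This will also be analysed using secondary data from hospital-IT-systems", together with statutory health insurance data. The section on documentation and data storage says that these data will be applied for. Neither section says which source decides if the two disagree. For medication, the Analysis section says: "pharmaceutical problems in both intervention arms of the study will be statistically compared with the patients in the control group".

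**The concern.** The instrument is the same in every arm, but the length of time over which it asks patients to remember is not. In the intervention arms, follow-up use is recorded in short pieces by the people who deliver the intervention. In the control arm it is recorded once, for the whole follow-up. If patients forget contacts as the window lengthens, more are lost in the control arm. Double-counting one visit at two adjacent calls would push the same way, towards more apparent contacts under intervention.

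Randomisation does not protect against this, because the difference arises after allocation. Analysing change from baseline does not help either. Baseline appears to use a 6-month window in all arms, so the window shortens only under intervention. Extra calls also tie the window length to how the patient is doing.

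At stake is the direction of the self-reported result: a real fall in contacts could look like no effect, or no effect could look like an increase.

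**Working it through.** The article gives no figure for this outcome (no expected contact rate, power or recall accuracy), so there is nothing to reproduce. The windows follow from the schedule. The size of the bias needs assumptions, which are marked as such.

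**1. Recall windows (from the Study intervention and Evaluation Interviews sections)**

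- Scheduled calls: 4 weekly + 5 monthly = 9, taking month 1 as 4 weeks. The first call looks back over the preceding 6 months, so about 8 calls cover follow-up.
- Interval between calls: 1 week in month 1, then (26 − 4)/5 = 4.4 weeks (or 26/6 = 4.3 weeks for a calendar month). It is shorter if calls are added.
- Control window: about 26 weeks. This is inferred from the same questionnaire being used only at baseline and 6 months. The inference is firm, but the window is not stated.
- Ratio of windows: 26/4.4 = 5.9 up to 26/1 = 26.

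**2. Effect on the rate ratio**

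Let r be the completeness of 6-month recall relative to short recall (assumed, not from the documents). Then observed rate ratio = true rate ratio / r.

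| r (assumed) | True ratio 1.00 appears as | True ratio 0.80 appears as |
|---|---|---|
| 0.95 | 1/0.95 = 1.05 | 0.80/0.95 = 0.84 |
| 0.90 | 1/0.90 = 1.11 | 0.80/0.90 = 0.89 |
| 0.80 | 1/0.80 = 1.25 | 0.80/0.80 = 1.00 |
| 0.70 | 1/0.70 = 1.43 | 0.80/0.70 = 1.14 |

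At r = 0.80 a true 20% reduction disappears; at r = 0.70 it is reversed.

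**3. Effect on the false-positive rate, one intervention arm against control**

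Inputs: 120/3 = 40 per arm, or 40 × 0.80 = 32 if the roughly 20% loss reported for controls applied to each arm. Assumed: mean μ of 5 or 10 contacts in 6 months, and negative binomial variance μ + μ²/k with k = 1 or 2. With no true effect:

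- shift d = μ(1 − r)
- SE = √[(v₁ + v₂)/n], with v₁ taken at mean μ and v₂ at mean rμ
- rejection rate = Φ(d/SE − 1.96) + Φ(−d/SE − 1.96)

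Example: μ = 5, k = 1, n = 32, r = 0.80. Then d = 1, v₁ = 5 + 25 = 30, v₂ = 4 + 16 = 20, SE = √(50/32) = 1.25 and d/SE = 0.80. The rejection rate is Φ(−1.16) + Φ(−2.76) = 0.126.

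Over all combinations, against a nominal two-sided 5%:

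| r (assumed) | False-positive rate |
|---|---|
| 0.95 | 5–6% |
| 0.90 | 7–9% |
| 0.80 | 13–24% |
| 0.70 | 24–51% |

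**4. After the change**

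With one source or one equally complete window in all arms, r = 1. A true ratio of 1.00 is then observed as 1.00, and the rate returns to 5%.

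**The case against.** Four points weigh on the other side.

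- **An arm-neutral source is already planned.** A reader might infer that the secondary comparison as a whole is biased by measurement. The documents do not support that. The same comparison is planned on hospital and insurer records, which depend neither on memory nor on arm, and the article does not rank self-report above them. This stands and limits the point to the interview-based counts. It does not dispose of the point, because the records are only to be applied for and nothing makes them decisive.

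- **The size is assumed.** No recall figure appears in the article, one range is applied alike to outpatient visits and hospital stays, and at r = 0.95 the distortion is close to negligible. This stands. It is also not stated that the call counts will be summed. Summing is the natural reading of successive windows, but the construction of the variable may be left to an analysis plan that is not shown.

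- **Medication.** A reader might infer that medication problems must look far more frequent under intervention, because patients are asked about nine times rather than once. That does not follow. The article does not define pharmaceutical problems, states no endpoint of any problem over all calls, and gives no ground for treating repeated answers about the same drugs as independent. Of the medication questions, only those on dosage change are tied to the previous call; those on effect and regularity have no stated recall period. What remains is that a between-arm comparison needs the same reference period in each arm.

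- **Rank of the outcome.** Contact frequency is a secondary objective, and the windows at issue are stated for contacts and stays, not for the psychopathological outcomes. This stands and lowers the severity.

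**Conclusion.** The concern holds for the self-reported comparison of contacts and inpatient stays. The plan as written measures them over windows of about 1 to 4.4 weeks in the intervention arms and about 26 weeks in controls. If longer recall is less complete, contacts are under-counted more in controls. They need not be under-counted only there, since short recall can miss events too.

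The asymmetry rests on the text plus one firm inference, the control window. The magnitude rests wholly on assumption: relative completeness of 0.95 to 0.70 gives an apparent rate ratio of 1.05 to 1.43 when there is no effect. The record-based comparison is not exposed to this, and no figure for medication problems can be supported. Severity: should-fix, not must-fix.

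**What to change.** 1. **Analysis section:** name the insurer and hospital records as the main source for the between-arm comparison of contacts and stays wherever they are obtained, with self-report as support.
2. **Study intervention and Evaluation Interviews sections:** for patients still in follow-up, ask all three arms the identical question about the past 6 months at the final interview, and use only that answer for the self-reported comparison. Keep the call-by-call counts for monitoring and for description within the intervention arms.
3. **Medication, if compared between arms:** use only month-6 items with the same reference period in all arms, either current regularity and perceived effect, or dosage change since discharge. Taking the month-6 dosage question as it stands would reverse the asymmetry: about one month back under intervention against about six months in controls.

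**Cost.** A few minutes in the last intervention call and some rewording. Recall over 6 months is less precise than summed short recall, and having already reported events at earlier calls may still help intervention patients remember, so the common question narrows the gap but may not close it. The section on recruiting and participants shows that the first patients had already reached their final interview. For those who have finished, only the records can supply a common measure, so applying for them should not wait. Coverage of the records needs checking, since they come from various hospitals in the region and from statutory insurers.

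### Self-reported service contacts after baseline are recalled over about 1 to 4.4 weeks per call in the intervention arms but over about 6 months in the control arm, so that part of the secondary comparison is not like for like

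*Protocol article*

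**What the plan says.** The protocol article (Study intervention) has the nurse ask about physician contacts and inpatient stays in the standardised part of each call. The look-back period changes after the first call: "During the first telephone call, contacts with physicians and inpatients stays are assessed for the last 6 months", and then "during the following contacts for the time since the last telephone contact". The schedule is: "The first month, the telephone contacts take place once a week, thereafter, once a month". More calls are possible if needed. The second intervention arm receives "telephone contacts with the same content as the telephone contacts of the first study arm", so its look-back periods are the same.

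Under Evaluation Interviews, for patients in the intervention arms, "evaluation data is collected mainly during the standardized part of the telephone calls", and contacts with health services are listed among those data. Controls have "a baseline interview and a follow up interview after 6 months which includes the same standardized questionnaires as the intervention groups".

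Research objectives makes the effect on contact frequency the secondary objective. The Analysis section compares it between the intervention arms and control and adds a second source: "This will also be analysed using secondary data from hospital-IT-systems of various hospitals within the region of Western Pomerania", together with statutory health insurers. Documentation, data storage and data security says that these data will be applied for.

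**The concern.** The follow-up count is built differently in the arms being compared. For an intervention patient it is a sum of counts, each recalled over a short interval. For a control patient it is one answer covering the whole follow-up. If people forget more contacts over six months than over a few weeks, equal true use gives a lower recorded count in control.

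Randomisation does not protect against this, because the difference is in measurement and follows the assigned arm. Baseline adjustment does not help either: the window is 6 months at baseline and shortens at follow-up in the intervention arms only.

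The article motivates the concept partly by the hope of relieving the existing health care system. A bias that inflates apparent use in the intervention arms works directly against detecting that effect.

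This is not a detail that an analysis plan could supply later. If the intervention arms are never asked the 6-month question at follow-up, no model can recreate the answer.

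**Working it through.** The article gives no effect size, recall figure or utilisation figure for this outcome, so there is no stated number to reproduce.

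**Step 1: recall windows (from the stated schedule).** Take 6 months as 26 weeks, with four weekly intervals and five equal intervals after that.
- Length of each later interval: (26 − 4) / 5 = 4.4 weeks.
- Check: 4 × 1 + 5 × 4.4 = 26.
- Mean window, weighted by the follow-up time it covers: (4 × 1² + 5 × 4.4²) / 26 = 100.8 / 26 = 3.9 weeks.
- Control: one window of about 26 weeks. Ratio: 26 / 3.88 = 6.7.

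The control window is not stated in words. It is inferred from the two-interview schedule, and both wordings of the question (the past 6 months, or since the previous contact) lead to about 6 months.

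If the first call of month 1 is itself the baseline call, there are three weekly intervals and five of (26 − 3) / 5 = 4.6 weeks. The weighted mean is then (3 + 5 × 4.6²) / 26 = 108.8 / 26 = 4.2 weeks and the ratio about 6.2. The conclusion is the same.

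**Step 2: illustrative size (assumption, not from the documents).** Let the chance of reporting a contact *t* weeks later be exp(−k·t). A window of length T then captures

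c(T) = (1 − exp(−k·T)) / (k·T).

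Set k so that c(26) equals an assumed capture in control. The capture in the intervention arms is [4 × 1 × c(1) + 5 × 4.4 × c(4.4)] / 26. The observed rate ratio is the true ratio × capture(intervention) / capture(control).

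| Capture at 26 weeks (loss) | k | Capture, intervention | True 1.00 appears as | True 0.80 appears as |
|---|---|---|---|---|
| 95% (5%) | 0.0040 | 0.992 | 1.045 | 0.836 |
| 90% (10%) | 0.0083 | 0.984 | 1.094 | 0.875 |
| 80% (20%) | 0.0179 | 0.966 | 1.208 | 0.966 |
| 70% (30%) | 0.0293 | 0.946 | 1.351 | 1.081 |

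Example: at 20% loss, 0.966 / 0.80 = 1.208, and 0.80 × 1.208 = 0.966. Under this model a true reduction of 20% almost vanishes at 20% loss and reverses at 30%. With the alternative interval count from step 1, the fourth column runs from 1.044 to 1.345.

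**Step 3: effect of equal windows.** With the same window in every arm, capture(intervention) / capture(control) = 1 and the distortion is 1.00, provided that recall is otherwise equal between arms.

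**The case against.** The strongest reply is that the article already plans a recall-free analysis of the same comparison, using hospital and insurer data. That stands in part. A reader might infer that the whole secondary comparison is compromised. The documents do not support this, because only the self-reported part carries the recall difference. But the record analysis is described as additional, its data have still to be obtained, and the hospital source covers only some hospitals in the region. It mitigates the problem without curing the self-reported comparison.

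Second, no document shows how patients recall contacts. Forgetting is a reasonable expectation, but older visits can also be moved into a long window, and repeated questioning can lead to over-reporting. This stands: the unequal windows are a fact of the plan, while the direction and size of the bias are assumptions.

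Third, the effect may be small. Take an assumed mean of 6 physician contacts per 6 months (negative binomial, dispersion k = 2), 40 intervention and 32 control patients, no true effect, and 5% of contacts lost in control relative to short recall. A two-sided 5% test then rejects in about 5.9% of trials, close to nominal. For rarer inpatient stays (assumed mean 0.3 to 1, dispersion k = 1), 5% to 10% loss gives about 5% to 6%. This also stands, and is why no false-positive rate is put forward as the main result.

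Fourth, a new month-6 question comes too late for some patients. Recruiting and participants reports that recruitment began in September 2009 and that the first participants had already been contacted for their final interview. This is correct, and the fix allows for it.

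**Conclusion.** The point holds for the self-reported part of the secondary comparison. As the article describes data collection, both intervention arms recall follow-up contacts and stays over about 1 to 4.4 weeks and the control arm over about 6 months, a window roughly six to seven times longer. Neither randomisation nor baseline adjustment removes a difference linked to arm in this way.

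If longer recall loses contacts, and the 6-month loss is 5% to 30%, a true rate ratio of 1.00 would appear as about 1.05 to 1.35, which could hide a real reduction. This range rests on an assumed exponential loss of recall, and the documents give no figure with which to narrow it. The effect is likely to be smaller for inpatient stays than for routine visits. It would be too strong to say that the trial will report a spurious rise in health care use: the direction is plausible but not established.

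The change is worth making because it is cheap and because the missing question cannot be recovered at analysis.

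**What to change.** 1. **Same question in all arms.** At the month-6 contact in all three arms, ask about physician contacts and inpatient stays over the past 6 months in the same words as at baseline. Use this item for the self-reported comparison with control. Keep the per-call counts for description within the intervention arms.

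2. **Patients already past month 6.** Do not mix summed per-call counts from these intervention patients into the main self-reported comparison without a flag. Report them in a sensitivity analysis and rely on record data for these patients.

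3. **Record data.** In the Analysis section, state that where hospital and insurer data are obtained for all arms alike, they are the main source for the between-arm comparison of the contacts they cover, with self-report as supportive. State the coverage limits: only some hospitals in the region take part, and under Data protection the data of patients who withdraw consent are not used.

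**Cost.** An existing question block is repeated at the last call, a few extra minutes per intervention patient, and a short text is added to the Analysis section. The 6-month count is less accurate in absolute terms than the summed short-interval counts, but its window is the same in every arm. Intervention patients may still recall slightly better because they were asked before, so some imbalance may remain.
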